### Ethics, consent and data management

The study received ethical approval from Waterford Institute of Technology Research Ethics Committee (REF: WIT2018REC0010). This study has also been registered with the ‘International Standard Randomised Controlled Trial Number’ registry (ISRCTN79921361). During Shed visits, all participants have the details of the research clearly explained to them through verbal and written instruction and informed written consent is obtained by a member of the research team prior to participation in the research. Confidentiality of participants is ensured through the study’s compliance with Waterford Institute of Technology’s protection policy. Namely, all personally identifiable materials, such as consent forms, will be stored securely within the Institute. These will be stored separately from the transcribed research data and questionnaires, and only accessible by named researchers. All data sets will be kept on a password protected computer. Personal identifiable data will be retained for 5 y and then appropriately destroyed. Research data will be fully transcribed and anonymised, all details on identity, will be removed and replaced with deidentified information or pseudonyms. All enrolled participants will be allocated a unique study ID and the information linking their ID to their personal information will be held securely at Waterford Institute of Technology. All intervention content will be run under the guidance and training of IMSA by qualified external partners. Therefore, the risk to persons is not directly linked to this research. However, all SFL partners are adequately insured and qualified to run elements of SFL and engage in a screening process with participants to assess their ability to partake in the intervention for safety purposes. Screening elements of SFL will be run by registered nurses from the Irish Heart Foundation. Other practitioners working directly with participants are trained in first aid and also will complete Guidance training for working effectively within the environment of the Sheds. Topics covered in discussions or during questionnaire administration leave a small but important risk of participants becoming distressed. In case of such an event the distress of the participant will be ascertained, and the participant offered a break from the interview or to suspend the interview as appropriate. If a participant becomes distressed the researcher will stay with them until their distress reduces, or if their distress persists, the researcher will signpost them to an appropriate community support service. The researcher will report any issues of concern to the project supervisors and the IMSA.

### Effectiveness- implementation evaluation design

The SFL study adopts an implementation science focus. This approach strives to incorporate a broader scope than traditional clinical effectiveness alone; to focus not only on individual or participant level but also on how service provider, organisation, and wider systems impact implementation [36]. Successful implementation should be considered in light of a variety of factors including the effectiveness of the intervention to be implemented alongside implementation outcomes [41]. For these reasons, a hybrid type-two effectiveness-implementation study design was chosen. This means dual testing of effect and implementation outcomes of SFL in order to pragmatically promote translation into the real world context from the outset while also providing more valid estimates of potential effectiveness in the implementation setting of the Sheds [42]. In order to assess implementation outcomes and address barriers and facilitators to effective implementation, a community-based participatory research approach was adopted to involve key stakeholders across implementation levels [38]. Mixed methods are used to assess both implementation and effectiveness outcomes, which are described in detail in the following sections (See Table 2). The following sections outline the research design. Part 1 details how effectiveness of SFL is evaluated and Part 2 describes how the SFL implementation is evaluated.

**Table 2 Tab2:** SFL Effectiveness-Implementation Hybrid design

Evaluation	Research Question	Research Methods & Data collection approaches	Tools & Frameworks	Targeted Outcome
**Implementation**	What are the facilitators and barriers that impact implementation and sustainability of SFL across the individual, provider, organisation and wider systems level?	Qualitative Participatory Research Focus groups, Interviews (Hybrid approach of thematic deductive and inductive analysis) Ethnography Stakeholder meetings	PRACTIS guide (PRACTical planning for Implementation and Scale-up) CFIR (Consolidated Framework for implementation research) Semi-structured topic guides	Acceptability Adoption Appropriateness Feasibility Fidelity Implementation Cost Penetration Sustainability
	What is the process by which the SFL model is developed and implemented in order to effect maximum penetration, adoption and acceptability among key stakeholders?	Qualitative Participatory Research Focus groups, Interviews Ethnography Stakeholder meetings Quantitative Recording attendance (providers) & Self-reported attendance at follow-up (participants)	PRACTIS guide (PRACTical planning for Implementation and Scale-up) CFIR (Consolidated Framework for implementation research) Attendance and membership records Semi-structured topic guides	Penetration Adoption Acceptability
	How does the Partnership and Capacity building focus of SFL contribute to the implementation and scale-up of the programme?	Qualitative Participatory Research Interviews Stakeholder meetings Capacity Building Workshops	PRACTIS guide (PRACTical planning for Implementation and Scale-up) CFIR (Consolidated Framework for implementation research) Semi-structured topic guides	Acceptability Adoption Appropriateness Feasibility Sustainability
	Is the SFL implementation approach cost-effective?	Quantitative Cost Gathering Assessment of cost using Quality Adjusted Life Years	The SF6D	Implementation Cost Feasibility Sustainability
**Effectiveness- Implementation**	Does participation in Sheds for Life improve health knowledge attitudes, outcomes and behaviours among participants?	Pragmatic controlled Trial Quantitative Questionnaires administered at baseline, 3, 6 & 12 months Qualitative Focus groups, ethnography, key informant interviews	Core outcome tools Self-reported Health Rating Seeking health information rating 7-item Short Warwick- Edinburgh Mental Wellbeing Scale (SWEMWBS) 5- point Likert Scales assessing; comfort having a conversation about mental health, understanding mental health and identifying practical supports 3-Item UCLA Loneliness Scale. Rated on a 3- point scale. Higher scores equal increased loneliness ONS 11-point Scales 0–10 Life satisfaction and life worth 8 point scales 0–7 physical activity and walking measure The 9-item self-efficacy for exercise scale (SEE) Close support, belonging, trust Alcohol, smoking & fruit & vegetable consumption Cooking frequency, cooking style and 12 measure scale measuring confidence constructs in relation to cooking Supplementary outcomes: Questions measuring changes in confidence and knowledge in relation to supplementary components developed in collaboration with provider organisations Qualitative tools Semi-structured topic guides	Quantitative Core outcomes Subjective Wellbeing Help-seeking Physical Activity Mental Wellbeing Diet & Cooking skills Social Capital Self-efficacy Quantitative Supplementary outcomes Diabetes Awareness, SafeTALK suicide prevention, Digital Literacy, Oral Health, Cancer awareness, CPR Qualitative outcomes Changes in attitudes and behaviours Acceptability Adoption Appropriateness

### Part 1: evaluating the effectiveness of SFL-research design

#### Overview

Phase one of SFL encompassed the first delivery of the programme in Sheds. Following assessment of the implementation environment, namely the capacity and resource constraints of provider organisations to deliver SFL along with the nuances, ethos and autonomy of the inner (Sheds) setting, the SFL 10-week intervention was implemented on a phased basis across two cohorts comprising two counties in each cohort with a view to delivering Phase 2 as a single cohort across a further four new counties (i.e. Phase 1 (4 counties, two cohorts); Phase 2 (4 counties, one cohort); see participants and sampling). A mixed methods approach was applied to assess the impact of SFL Phase 1 testing on the biopsychosocial health of participants up to 12 months. This consisted of focus groups, interviews and questionnaires assessing health outcomes.

#### Participants and sampling

Respecting the autonomous and informal environment of the Sheds is an important factor in delivering health promotion through Sheds [27, 33]. Therefore, Sheds are recruited to participate in the SFL programme and evaluation via purposive sampling using an expression of interest process with the objective to deliver SFL in a diverse range of Shed settings (small/large, urban/rural). All adult males in the Sheds setting were eligible to participate in the study providing they had good proficiency of the English language and could give informed consent. A sample size estimation was undertaken using G*Power 3.1.9.2 software using physical activity (PA) as the key outcome measure, whereby it was calculated that 106 participants would be required for a trial in which participants were individually randomised (the decision to use PA as the primary outcome measure was determined through consultation with Shedders who requested that PA be a key focus of SFL during the initial pilot phase). However a clustered design in which SFL was delivered to small clusters of men within Sheds was more preferable to honour the Shed ethos whilst also ensuring a wide geographical spread. For this reason a design with circa 20 men in each cluster was estimated. A previous study with middle-aged men suggested that this design effect is ~ 2.4, thus increasing the sample size required to 255 [47]. Allowing for a 20% dropout based on a sample size estimation, the final total required was 306 or 15 clusters. In the event of low participation within clusters, it was decided that SFL would be targeted at clusters with similar representation. In Phase 1, 421 Shedders participated across 22 clusters and these were divided into two cohorts. Whilst delivery occurred in the first cohort (*n* = 12 clusters; *n* = 212 Shedders) a wait list control cohort served as a comparator (*n* = 3 clusters; *n* = 89 Shedders) and these were a subset of the second cohort (*n* = 9 clusters, *n* = 209 Shedders). Fourteen clusters were in urban areas and 8 were in rural areas across counties; Kildare (in Ireland’s mid-east region with a population of ca. 222, 504), Waterford (in Ireland’s south-east region with a population of ca. 116,176), Limerick (in Ireland’s south-east region with a population of ca. 194,899) and Louth (in Ireland’s mid-east region with a population of 128, 884) [48]. Participants were recruited for Phase 1 across Waterford and Kildare in March to May 2019 and Limerick and Louth in September to December 2019. Participants for Phase 2 will be recruited from September to December 2021 (recruitment was postponed until this date due to COVID-19 restrictions).

Purposive sampling was also used to conduct formal focus groups (*n* = 8) with participating Sheds in Phase 1. This qualitative study seeks to gather a diverse representation of Shedders’ experiences of SFL to compliment quantitative findings including changes in knowledge, attitudes and behaviours. Informal short interviews (*n* = 16) were also conducted ad-hoc during Shed visits in Phase 1 to further inform Shedders’ experiences of SFL.

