#### Evaluating the effectiveness of SFL- data analysis

Questionnaire data is analysed using Statistical Packages for the Social Sciences (SPSS V 24). Descriptive statistics for each variable are calculated to inform participant characteristics. Intervention effect on health and wellbeing outcomes are determined by comparing the change scores from baseline to 3, 6 and 12 months, comparing data using inferential tests to identify significant differences set at *p* = 0.05. Analysis of subgroups based on criteria such as; Shed size location and timing of the intervention, will also be performed to identify significant differences in intervention effect between groups. Outcome data obtained from all participants are included in the data analysis, regardless of adherence to SFL. The intervention effects will be assessed at 3, 6 and 12 months based on those who completed follow-up at these time points. Assuming a worst case scenario for absentees i.e. that absentees failed to achieve a significant improvement in core health outcomes (physical activity, diet, mental wellbeing, subjective wellbeing, social capital and help-seeking), these worst- case scenario analyses will reflect the intention to treat principle. The numbers who achieved significant improvement at 3, 6 and 12 months will be presented as a percentage of those who were tested at these follow-up points. For the initial intervention effect worst-case scenario, the numbers who achieved significant improvements at 3 months will be presented as a percentage of those who were tested at baseline. The worst-case scenario for maintenance of this initial intervention effect will present the numbers who achieved significant improvements at 6 and 12 months as a percentage of those who were tested at the 3 month follow-up. Observed success rates will be compared between the intervention and comparison group in waiting using Chi-Square analysis.

A hybrid analytic approach of inductive and deductive analysis is applied to the participant transcripts. This means that whilst implementation frameworks are applied to inform implementation outcomes, the analysis process will remain open to findings that may emerge outside of those pre-set domains to allow assessment of intervention effect. In these circumstances, inter-rater reliability is used to cross-check coding strategies and interpretations are negotiated to agree on a ‘master’ code list.

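### The 20% dropout allowance is added to 255 (giving 306) rather than divided out (giving 319), so the stated target retains about 245 men, not 255

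*Protocol article*

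**What the plan says.** The calculation is in the protocol article under Participants and sampling, with physical activity as the outcome. It has three steps.

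- Start: "it was calculated that 106 participants would be required for a trial in which participants were individually randomised".
- Clustering: "a design with circa 20 men in each cluster was estimated", and from an earlier study in middle-aged men "this design effect is ~ 2.4, thus increasing the sample size required to 255".
- Attrition: "Allowing for a 20% dropout based on a sample size estimation, the final total required was 306 or 15 clusters".

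The same section reports what was achieved: "In Phase 1, 421 Shedders participated across 22 clusters and these were divided into two cohorts". For the controlled comparison, 212 men in 12 clusters received the programme while "a wait list control cohort served as a comparator", with 89 men in 3 clusters. No other part of the article restates or corrects the 306.

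**The concern.** The last step should turn a number needed at analysis into a number to enrol. If 255 is needed and 20% of those enrolled are expected to be lost, the enrolment target must still hold 255 after the loss. Adding 20% to 255 does not do this, because the loss is taken from the larger, enrolled number.

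The step matters here because the data analysis section bases the effects at 3, 6 and 12 months on the men followed up at those times. What is at stake is the accuracy of a headline design figure that readers will use to judge recruitment. It could also be carried forward: Phase 2 recruitment was still to come when the article appeared, although the article does not say that this calculation applies to Phase 2.

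**Working it through.** **Inputs, all from Participants and sampling:** 106 men under individual randomisation; design effect about 2.4; clusters of about 20; dropout 20%; stated results 255, 306 and 15 clusters. The effect size, standard deviation and power behind the 106 are not given. The 106 is taken as stated, and the check does not depend on them.

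**1. Clustered requirement.** 106 x 2.4 = 254.4, rounded up to 255. This reproduces the plan's figure.

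**2. How 306 arises.** 255 x (1 + 0.20) = 306, an exact match. Division gives 255 / (1 - 0.20) = 318.75, so 319, which does not match.

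**3. Does the order of steps explain it?** No. Applying dropout before the design effect gives 106 / 0.80 x 2.4 = 318 by division and 106 x 1.20 x 2.4 = 305.3 by multiplication. The same two answers appear.

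**4. What 306 retains.** 306 x 0.80 = 244.8. The shortfall is 255 - 244.8 = 10.2 men, and 10.2 / 255 = 4.0%.

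**5. Dropout that 306 can absorb.** 1 - 255 / 306 = 16.7%.

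**6. Check of the corrected figure.** 319 x 0.80 = 255.2, which meets 255.

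**7. Clusters.**

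| Total | Divided by 20 | Average size in 15 clusters |
|---|---|---|
| 306 | 15.3 | 20.4 |
| 319 | 15.95 | 21.3 |

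Fifteen clusters averaging 20.4 men hold 306, which fits a cluster size given only as approximate. For 319 the natural count is 16: 16 x 20 = 320, and 320 x 0.80 = 256.

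**8. Against actual numbers.** All of Phase 1: 421 men in 22 clusters, above 306 and above 319. Controlled comparison: 212 + 89 = 301 men in 12 + 3 = 15 clusters, below 306 and below 319.

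**9. Size in power terms, under assumptions.** Suppose the 106 was set for 80% or 90% power at two-sided 0.05. The article gives a significance level of 0.05 in its analysis section, but neither the power nor the sidedness. Holding the design effect at 2.4, power at 244.8 men is the normal probability below (1.96 + z) x sqrt(244.8 / 254.4) - 1.96, where z is 0.84 or 1.28. This gives about 78.5% or 88.9%.

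**10. If the design effect is allowed to shrink with the clusters.** Assume equal clusters and that 2.4 applies at 20 men. The implied intracluster correlation is (2.4 - 1) / (20 - 1) = 0.074. With about 16 men left per cluster the design effect is 1 + 15 x 0.074 = 2.1, and the requirement is about 106 x 2.105 = 223. The 244.8 retained exceeds that.

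**The case against.** The best defence is that the error has little practical effect.

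- **The inputs are approximate.** A design effect of 2.35 to 2.45 gives a requirement of about 249 to 260 (106 x 2.35 = 249.1; 106 x 2.45 = 259.7), a spread of about 11 men, as wide as the shortfall. This stands as a comment on size. It does not rescue 306, since 244.8 lies below even the lower end, and the plan itself fixes the requirement at 255.
- **Attrition within clusters lowers the design effect** (step 10), so the men retained may still be enough. This also stands, although the article does not make the argument. A reader might infer that the study is underpowered, or that the retained men are worth only 244.8 / 2.4 = 102 individually randomised men instead of 106. The document does not support that: the equivalence holds the design effect at 2.4 while the clusters shrink, and the planned power is not stated.
- **The cluster count is not wrong.** A reader might infer that 306 men need 16 clusters because 15 x 20 = 300. But the article says about 20, never exactly 20, and never sets a target of 300. Fifteen clusters of 20.4 men are consistent with its wording.
- **Recruitment is settled.** Enrolment of 421 clears both figures and the 301 in the controlled comparison miss both, so correcting the total changes neither headcount judgement. This stands. The only comparison that shifts is the cluster count in the controlled comparison, where 15 equals the stated number and is one below 16. That is a weak point when the cluster size is itself approximate.

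None of this makes 306 the right answer to the question the sentence sets.

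**Conclusion.** The stated total is wrong on the plan's own inputs. To retain 255 men after 20% dropout the target is 319, not 306, a difference of 13 men. With 306 enrolled, about 245 remain, roughly 10 men or 4% short, and the allowance actually built in is about 16.7%. This rests only on the article's 255 and 20%, with dropout meaning a share of the men enrolled.

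The severity is minor. The documents do not show a second error in the number of clusters, a demonstrated loss of power, or a need for more recruitment.

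**What to change.** Correct one sentence in Participants and sampling, in either of two ways:

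- state the target as 255 / (1 - 0.20) = 319 participants, or 16 clusters of about 20 men; or
- keep 306 participants in 15 clusters and state that this allows for about 17% dropout.

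If the calculation is reused for Phase 2, carry the corrected form forward. The cost is a reworded sentence. Neither the analysis nor Phase 1 recruitment changes.

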#### Evaluating the effectiveness of SFL- data collection

Questionnaires are administered to participants by a research team member trained in data collection procedures to ensure standardised measurement and questionnaire administration. Questionnaires are administered one-to-one in the Sheds setting to account for potential literacy issues, prevent respondent burn-out, limit missing data and build rapport and trust between the researchers and Shedders. To also minimise missing data, participants will be contacted by the IMSA in the days before the research team visit the Sheds to perform data collection. Due to the informal nature of the Sheds, absence of data for a participant does will not necessarily indicate dropout from SFL. During 6 and 12 month follow-up in Phase 1, Cohort 2 were experiencing COVID-19 restrictions and therefore questionnaires were administered via phone in order to promote participant retention and complete follow-up. The questionnaire was designed via a consultation process with stakeholders involved in the design and delivery of SFL with a view to optimising acceptability for SFL participants and also SFL providers who were interested in evaluating their individual components of SFL. Participant demographics are recorded at baseline and include date of birth, living arrangements, educational attainment, employment status relationship and ethnicity. Participants are also asked how long they had been a Shed member and how often they attend the Shed. Core health and wellbeing outcomes measured at all-time points up to 12 months consist of; subjective wellbeing, help-seeking, physical activity, mental wellbeing, diet and cooking skills, social capital and self-efficacy. Participants are also asked how often they seek information about their health.

Self-rated health is measured using a single question Likert scale with high reliability among older men [49]. The single-item PA measure is used to record PA levels [50]. The Self-Efficacy for Exercise Scale (SEE) is used to measure physical activity self-efficacy [51]. Life worth and satisfaction are recorded using the Office of National Statistics subjective wellbeing 11-point scales [52]. Mental wellbeing is measured using the Short Warwick-Edinburgh Mental Wellbeing Scale (SWEMWBS) with raw to metric score conversion where a change of 2+ is considered relevant [53]. Loneliness is measured at all-time points using the UCLA 3-item scale measuring three dimensions of loneliness; relational connectedness, social connectedness and self-perceived isolation, with participants also asked at baseline to retrospectively rate their loneliness prior to joining the shed [54]. Social Capital is measured based on relevant recommendations from WhatWorksWellbeing [55], capturing trust, belonging and close support. Interpersonal trust is measured using the Office of National Statistics 11-point scale [52]. Lifestyle behaviours are also recorded - smoking (number smoked per day) and alcohol consumption (days drinking and units consumed per drinking session). Assessments of cooking and healthy eating behaviours are developed in conjunction with the partner organisation delivering the Healthy Food Made Easy component of SFL. Participants are asked about their levels of daily fruit and vegetable consumption, cooking style, cooking frequency and willingness to cook. Confidence constructs around cooking and healthy eating are measured via a 12 item Likert scale ranging from “not at all confident” to “very confident”. The questions were adapted from a protocol for community-based cooking interventions which were developed at a lower literacy level with varying levels of literacy among participants in mind [56]. The constructs used to assess cooking and healthy eating were previously validated [57] (See Table 2 for effectiveness outcome measures including optional components).

Semi-structured topic guides were developed for focus groups and short interviews. These were designed using a hybrid deductive-inductive approach applying implementation frameworks to assess implementation outcomes but also to allow room for exploring attitudes towards SFL, changes in knowledge and behaviours. A constant comparison process is being used to refine and adapt topic-guides to reflect new themes to be explored as SFL evolves across implementation settings.

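### At 6 months, and probably at 12, the planned intervention-timing subgroup cannot be separated from phone interviewing, COVID-19 restrictions and county pair, so a cohort difference there cannot be read as a difference in SFL effect

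*Protocol article*

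**What the plan says.** **Standard mode.** The data collection section for effectiveness says "Questionnaires are administered one-to-one in the Sheds setting to account for potential literacy issues", by team members "trained in data collection procedures to ensure standardised measurement and questionnaire administration".

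**Departure.** The same section reports that, at the 6- and 12-month follow-up of Phase 1, "Cohort 2 were experiencing COVID-19 restrictions and therefore questionnaires were administered via phone". No such change is stated for Cohort 1, or for either cohort at 3 months.

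**Cohorts.** Participants and sampling gives 212 men in the first cohort and 209 in the second, 421 in all. On dates and counties it says: "Participants were recruited for Phase 1 across Waterford and Kildare in March to May 2019 and Limerick and Louth in September to December 2019". The wait-list comparator (3 clusters, 89 men) is part of the second cohort and is described as serving while the first received delivery.

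**Analysis.** The data analysis section for effectiveness bases the effect on change from baseline to 3, 6 and 12 months and includes outcome data from all participants whatever their adherence. It adds: "Analysis of subgroups based on criteria such as; Shed size location and timing of the intervention, will also be performed". The stated purpose of these subgroups is to find significant differences in intervention effect between groups. Limitations mentions non-randomisation and self-report, but neither the mode change nor the restrictions.

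**The concern.** The article commits itself to reading a timing contrast as a difference in how well SFL worked. At the later visits the two cohorts also differ in how the questions were asked and in the conditions under which the men were living. Physical activity, the outcome used for sample size, and loneliness, belonging and trust could plausibly move under restrictions whatever SFL did.

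If the plan is followed as written, a shift from phone interviewing or restrictions could be reported as SFL working less well, or better, when delivered later. The Dissemination section says that Phase 1 results feed an interim impact report and inform Phase 2, so such a misreading would carry forward.

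**Working it through.** **1. The plan's own figure.** 212 + 209 = 421, which matches the stated Phase 1 total.

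**2. Share affected.** 209 / 421 = 49.6% of enrolled men. This is an enrolment share; the share of men actually followed up is not given.

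**3. What the timing contrast contains.** The article gives two counties per cohort and two recruitment periods, so Cohort 1 is taken as Waterford/Kildare and Cohort 2 as Limerick/Louth. At 6 months:

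| | Cohort 1 | Cohort 2 |
|---|---|---|
| Recruited | March–May 2019 | September–December 2019 |
| Counties | Waterford, Kildare | Limerick, Louth |
| Mode | in the Shed (no change stated) | phone |
| Restrictions | none stated | yes |

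Let s1 and s2 be the SFL effects in the two cohorts, k1 and k2 the county-pair influences, m the mode shift and r the restrictions shift. The difference in mean change is

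(s2 − s1) + (k2 − k1) + m + r.

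The indicators for cohort, county pair, mode and restrictions are the same column of zeros and ones. Only the sum can be estimated, and no covariate adjustment can isolate s2 − s1. No untreated group is described at 6 or 12 months from which m + r could be estimated.

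**4. What an all-participant change would contain.** With a common effect s and county influences set aside, the mean change is s + (209/421)(m + r) = s + 0.496(m + r).

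**5. Calendar check.** This assumes that visits are timed from recruitment, which the article does not say.

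| Visit | Cohort 1 | Cohort 2 |
|---|---|---|
| 3 months | June–August 2019 | December 2019–March 2020 |
| 6 months | September–November 2019 | March–June 2020 |
| 12 months | March–May 2020 | September–December 2020 |

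On this assumption Cohort 1's 12-month window lies within Cohort 2's 6-month window, which the article describes as restricted. The tail of Cohort 2's 3-month window reaches March 2020.

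**6. Illustration only.** The document gives no value for m + r. Assume shifts of 0.2, 0.3 or 0.5 SD, an identical true SFL effect and no county difference, 20% loss in each cohort, a two-sided 5% test, and the article's design effect of 2.4 allowed for. The numbers followed up are 212 × 0.8 = 169.6 and 209 × 0.8 = 167.2. The standard error in SD units is √(1/169.6 + 1/167.2) × √2.4 = 0.109 × 1.549 = 0.169.

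| Assumed shift (SD) | Move in all-participant change (SD) | Chance that timing is significant |
|---|---|---|
| 0.2 | 0.10 | 22% |
| 0.3 | 0.15 | 43% |
| 0.5 | 0.25 | 84% |

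These figures show how the mechanism works. They do not estimate the bias in this study.

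**7. Cost of separating cohorts.** √(421/212) = 1.41 and √(421/209) = 1.42, so intervals are about 1.4 times wider than combined ones, given equal variances and similar loss.

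**The case against.** The phone switch was forced, sensible and openly reported. Phone interviews can still be conducted by a trained interviewer, so the mode shift alone may be small. Detailed handling of mode and cohort is commonly left to an analysis plan, which is not shown. Timing is not defined in the article, and Phase 2 could add a further level.

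Most of this is fair, and it limits the point without removing it. The complaint is not that mode handling is missing. It is that the article states how the timing contrast will be interpreted, and no later analysis plan can make that interpretation identifiable from Phase 1 at 6 months. Phase 2 would be run in four new counties, with recruitment in late 2021, so it would also differ in place and period.

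Three stronger readings are tempting and not supported:

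- **That the plan pools the cohorts at 6 and 12 months.** A reader might infer this from the statement that all participants' data are included. That is an inclusion rule about adherence. No pooled estimate is specified, so pooling remains a possibility to guard against.
- **That the timing subgroup should go altogether.** The stated mode change applies to 6 and 12 months only; none is stated at 3 months.
- **That Cohort 1's 12-month data were also collected under restrictions.** The calendar allows it, but it rests on an assumed visit schedule, and the text names Cohort 2 only.

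**Conclusion.** The point holds for the later visits. At 6 months the Phase 1 timing contrast is completely aliased with interview mode, restrictions and county pair and cannot be read as effect modification. At 12 months the same is true unless Cohort 1 was by then also under restrictions. In that case restrictions would no longer cleanly divide the cohorts, but county pair would still differ, as would mode on the article's wording. Any all-participant change at 6 or 12 months would mix two conditions, with about half of the enrolled men (49.6%) in the phone-and-restrictions group.

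The conclusion assumes that timing means cohort, the only timing difference the article states within Phase 1, and that counties map to cohorts as set out in the working. The size and direction of any bias cannot be derived from the document. A reader might extend the point to the Shed-size and location subgroups, but nothing in the article ties Shed size or an urban/rural split to cohort or mode, so it does not reach them.

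**What to change.** 1. Present 6- and 12-month change by cohort. If a combined figure is shown, make it secondary and label it as mixed in mode and period.
2. Report the mode and actual date of each questionnaire. Check whether Cohort 1's 12-month visits fell under restrictions, and confirm that Cohort 2's last 3-month visits did not.
3. Limit the intervention-timing subgroup to 3 months, noting that county pair still differs there.
4. Relabel 6- and 12-month cohort differences as a contrast of cohort, mode, restrictions and county, not as a difference in SFL effect, and add this to Limitations.

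This changes wording and presentation and needs no new participants; it does require mode and visit dates to be available from study records. The cost is precision: cohort-specific intervals about 1.4 times wider than combined ones.
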